#### Data monitoring committee (DMC)

The main role of the DMC is to consider the data from any interim analyses and specifically to assess any safety issues (such as unexpected serious adverse events) that occur and report back to the TSC. The DMC membership is listed in Table 3. All members of the DMC are independent of the trial. The DMC will meet prior to the start of the trial and then one and two thirds of the way through the Trial or as required thereafter. The DMC will be expected to develop, in agreement with the investigators, a charter outlining their responsibilities and operational details.

**Table 3 T3:** Data monitoring committee membership

Name	Trial Role	Title	Affiliation
[name]	Chair	Professor of Cardiology	Nottingham
[name]	Statistician	Managing Director of Nottingham Clinical Research Group	Nottingham
[name]	Cardiology advisor	Consultant Cardiologist	Sheffield

#### Clinical event review committee

The Clinical Event Review Committee will review adverse events during the study and adjudicate them to ensure the events meet the definitions given. Each event will be independently adjudicated by two committee members. A third committee member will be called to adjudicate an event if agreement is not reached by two members. The adjudications will be blind to the knowledge of which arm of the trial the patients are in.

#### Study co-ordination

The study will be co-ordinated and managed by the Clinical Trials and Evaluation Unit (CTEU) a dedicated clinical trials department within the Royal Brompton Hospital. In addition to providing overall project co-ordination, the CTEU will assist in preparing the final protocol, the investigators' manuals, design the Case Report Forms (CRF), provide the randomisation service and design and instigate the data management system. The CTEU will ensure that the trial runs according to the pre-agreed timetable, recruitment targets are met, CRFs are completed accurately, compliance with relevant ethical and regulatory standards, and that all aspects of the study are performed to the highest quality. The CTEU will also assist in the training of investigators and co-ordinators at the start-up of the study and for performing monitoring procedures throughout. A smaller trial management team consisting of lead investigators at each site and CTEU will meet weekly by conference call.

### Regulatory issues

#### Study sites

Support for patient identification, study administration, data collection and follow-up will be provided to each participating site. Study site co-ordinators will be responsible for screening patients (and recording the data on a screening log), enrolling patients into the trial, providing a contact point for patients, liaising with CTEU, completing CRFs, arranging all follow up visits and measurements, recording adverse events, ensuring forms are sent to CTEU and that all edit queries are resolved.

#### Data collection

Each centre will be provided with a Protocol, Manual of Operations, questionnaires and patient CRFs. Data will be recorded onto two part NCR CRFs and the top copy sent to the CTEU at the times specified.

#### Investigators' responsibilities

Investigators must ensure that Local Ethics Committee approval has been obtained as well as Agreements signed off by their Institution prior to the start of the study. Investigators are responsible for performing the study in accordance with the European Clinical Trials Directive, the Medicines for Human Use (Clinical Trials) Regulations 2004, NHS Research Governance, MRC Guidelines for Good Clinical Practice in Clinical Trials (1998) and the Declaration of Helsinki guidelines. Investigators are required to ensure compliance to the protocol, CRFs and Manual of Operations. Investigators are required to allow access to study documentation or source data on request for monitoring visits and audits performed by the CTEU or any regulatory authorities.

#### Pre-study training visit

Before the study commences each centre will receive a training visit by CTEU. These visits will ensure that personnel at each site (including principal investigators, co-investigators, study site co-ordinator and pharmacists) fully understand the protocol, CRF and the practical procedures for the study.

#### Monitoring visits

At regular intervals during the study CTEU will perform monitoring visits to each centre. The purpose of these visits is to ensure compliance to the protocol and that ethical and regulatory guidelines are met. Source data verification and checking of essential documents will be performed. Monitoring visits also provide an opportunity for further training if required (eg new staff). Central review of study data will also be performed throughout the study.

#### Close out visit

At the end of the study each centre will receive a site visit from CTEU to resolve any outstanding edit queries or adverse events and to verify the correct storage of study documentation.

#### Regulatory framework and approval

This study is a randomised trial of a medicinal product in a new indication. The IL1-receptor antagonist is commercially available and approved for use in specific inflammatory conditions. As such the study will need to comply with the European Clinical Trials Directive and the Medicines for Human Use (Clinical Trials) Regulations 2004. An application will be made for a clinical trials authorisation (CTA) to the Medicines and Healthcare Regulatory Agency (MHRA) prior to starting the study. The study has been registered in the European Community with a Eudract number.

#### Study sponsor

The grant has been awarded to the University of Sheffield who will act as the main Sponsor of the study. The Sponsor's role is clearly set out in the European Clinical Trials Directive and NHS Research Governance documents. Research agreements will be held with the 4 collaborating groups: University of Edinburgh/Royal Infirmary of Edinburgh, University Hospitals of Leeds, Sheffield Hospitals NHS Trust and Royal Brompton and Harefield NHS Trust. The Clinical Trials and Evaluation Unit of the Royal Brompton will be responsible, on behalf of the University of Sheffield, for ensuring that regulatory compliance is carried according to the high standards expected.

#### Safety reporting

The University of Sheffield (Sponsor) has delegated responsibility for pharmacovigilance to the trial co-ordinating centre (Clinical Trials and Evaluation Unit (CTEU) of the Royal Brompton Hospital, London).

The CTEU will be responsible for recording all reported serious adverse events from investigational trial sites, reporting all serious adverse events to a constituted serious adverse events committee (SAEC) for review and expedited reporting of suspected unexpected serious adverse reactions (SUSARs) in accordance with statutory regulations. The SAEC will consist of one nominated investigator from each trial site who can provide clinical expertise to adjudicate serious adverse events and determine if they are SUSARs, and advise the CTEU whether expedited reporting is required.

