**Methods/design:**

Three centres in the UK are planning to recruit 186 Non-ST elevation myocardial infarction patients to receive either interleukin-1 receptor antagonist (Anakinra) or matching placebo. Patients will receive a daily subcutaneous injection of either study drug or placebo over a 14 day period. The primary outcome is area under the curve of high sensitivity C-Reactive Protein (CRP) over the first 7 days.

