#### Reporting of serious adverse events/reactions

The CRF will contain specific SAE reports relating to the SAEs/clinical outcomes listed above. The investigator will complete the SAE report in the CRF, including date of event, admissions, diagnosis details, date of discharge or death. Those SAEs considered a suspected unexpected serious adverse reaction (SUSAR) will be marked "possible SUSAR" on the SAE report. The investigator will also attach a discharge/medical summary and fax to the CTEU with the SAE report within 24 hours. Any other SAE not fitting the criteria above will be reported on the "other SAE" report in the CRF.

The CTEU will review all serious adverse event/reaction reports before sending an electronic copy to the SAEC for adjudication. All reported SAE/Rs will be adjudicated by the SAEC to assess the seriousness and causality between the IMP and/or concomitant therapy and serious adverse event/reaction. This assessment must take place within two working days upon receipt of the electronic copy of the form. If the SAEC judge the SAE/R to constitute a SUSAR, the CTEU will ensure expedited reporting procedures are followed.

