#### Suspected unexpected serious adverse reactions (SUSARS)

A SAR can be considered unexpected when the adverse reaction, the nature or severity of which is not consistent with the applicable product information. All suspected unexpected serious adverse reactions related to an IMP, which occur during the trial, are subject to expedited reporting.

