#### Reporting of SUSARs

The CTEU will unblind the SUSAR report before sending it electronically to the SAEC with the medical summary attached. The SAEC will review the report and summary within two working days and adjudicate whether the event constitutes a SUSAR. The SAEC will inform the CTEU of their decision to ensure expedited reporting procedures are followed if necessary.

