#### Unblinding

The treatment code must not be broken except in medical emergencies when the appropriate management of the patient necessitates knowledge of the treatment. Each pharmacy will keep a copy of the randomisation allocation list, in case unblinding is necessary. Should a SUSAR occur, the CTEU will unblind the patient and follow expedited reporting procedures.

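### Expedited reporting of an investigator's suspected unexpected reaction depends on the SAEC agreeing, although the protocol elsewhere makes every such suspected reaction subject to expedited reporting

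*Protocol article*

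**What the plan says.** The sponsor has "delegated responsibility for pharmacovigilance to the trial co-ordinating centre" (Protocol article, Safety reporting), which is the CTEU. On the SAEC, the same section states: "The SAEC will consist of one nominated investigator from each trial site who can provide clinical expertise". Its task is to "adjudicate serious adverse events and determine if they are SUSARs, and advise the CTEU whether expedited reporting is required".

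Under Reporting of serious adverse events/reactions, the investigator marks the SAE report as a possible SUSAR where the event is considered one. All SAE reports then go to the SAEC, which assesses seriousness and causality within two working days. The section continues: "If the SAEC judge the SAE/R to constitute a SUSAR, the CTEU will ensure expedited reporting procedures are followed".

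Reporting of SUSARs describes the same step for SUSAR reports, which the CTEU unblinds before the SAEC sees them: "The SAEC will inform the CTEU of their decision to ensure expedited reporting procedures are followed if necessary".

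The section that defines SUSARs contains no committee step: "All suspected unexpected serious adverse reactions related to an IMP, which occur during the trial, are subject to expedited reporting".

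Expedited reporting of SUSARs sets the time limits: 7 days for a fatal or life-threatening SUSAR and 15 days for any other, both to the MHRA and the ethics committee. Annual reporting provides a yearly report of suspected serious adverse reactions to the same bodies, which also goes to the DMC.

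**The concern.** Expedited reporting exists to act on suspicion before causality is settled. Here the suspicion of the investigator who reported the event is passed to a committee that reassesses causality, and the step that triggers expedited reporting is tied to the committee's answer. If that answer is no, nothing in the article keeps the report moving. Yet the general rule, which turns on the reaction being suspected, would require it to move.

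A CTEU officer holding a report marked as a possible SUSAR and a contrary SAEC opinion cannot tell from the protocol which instruction governs. If the SAEC's judgement is followed, the regulator and the ethics committee do not receive a serious, unexpected, possibly drug-caused event within the protocol's own time limits. This is a trial of a licensed drug in a new indication (Regulatory framework and approval), so early notice of unexpected reactions matters.

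**Working it through.** There is no figure to reproduce. The check is to follow one event through the text: a serious, unexpected event that the reporting investigator suspects was caused by study drug and that the SAEC then judges unrelated.

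| Step | Section | Result for this event |
|---|---|---|
| 1. Flag | Reporting of serious adverse events/reactions | Investigator marks the report as a possible SUSAR and faxes it within 24 hours |
| 2. Unblinding | Reporting of SUSARs | CTEU unblinds the SUSAR report and sends it to the SAEC |
| 3. Adjudication | Safety reporting; Reporting of serious adverse events/reactions | SAEC reassesses causality within two working days and decides that it is not a SUSAR |
| 4. Trigger | Reporting of serious adverse events/reactions; Reporting of SUSARs | Expedited procedures are tied to a positive SAEC judgement, so they are not triggered |
| 5. General rule | Suspected unexpected serious adverse reactions (SUSARS) | The reaction is serious, unexpected and suspected, so it is subject to expedited reporting |
| 6. Time limits | Expedited reporting of SUSARs | 7 or 15 days if step 5 governs; no limit applies if step 4 governs |
| 7. Next stated route | Annual reporting | Yearly report to the MHRA and ethics committee |

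Steps 4 and 5 give opposite answers for the same event, and no section ranks them.

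Could they be reconciled by holding that an event becomes a SUSAR only once the SAEC says so? Two details tell against that:

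- The instruction to the investigator covers events already considered suspected unexpected serious adverse reactions. The suspicion therefore exists at step 1. The SAEC's later view can add a second opinion, but it does not undo the fact that the reaction was suspected.
- Reporting of SUSARs calls the document a SUSAR report, and has it unblinded, before the SAEC has reviewed it.

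The SAEC's review time is not the problem, since two working days fit inside either limit. The gap arises only from a negative outcome.

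Nor is step 7 an assured substitute. It is annual, and the article does not say whether an event the SAEC has judged unrelated still counts as suspected for that report.

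**The case against.** The strongest reply is that the sequence is coherent: the investigator flags, the SAEC adjudicates, and the CTEU reports what has been adjudicated. The flag is only for a possible SUSAR, and the general rule does not say whose suspicion counts. The SAEC is said to advise, while the CTEU holds the delegated responsibility and must report in line with statutory regulations. The SAEC reviews all SAEs, so it can also pick up SUSARs that a site did not mark. The CTEU sees every SAE report, and a DMC independent of the trial assesses unexpected serious events.

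Part of this stands. The SAEC's review can add reports as well as hold them back, and the advisory wording leaves open that the CTEU could report anyway. But no section says that it may or should do so, and two sections tie expedited reporting to the SAEC's decision. DMC meetings one third and two thirds of the way through the trial, or as required thereafter, do not restore reporting within 7 or 15 days.

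Several stronger readings are tempting, and the documents do not support them:

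- **A vote that cancels reports.** A reader might infer that three site investigators vote and that two of them can block a report. No vote or majority rule is described. The number three is itself inferred, from "Three centres in the UK are planning to recruit 186" patients together with one SAEC member per site.
- **A missing rule for disagreement.** The Clinical Event Review Committee has one and the SAEC has none stated. Such a rule may sit in a charter or manual that the article condenses, so its absence is no finding.
- **A rival rule under Unblinding.** That section says "Should a SUSAR occur, the CTEU will unblind the patient and follow expedited reporting procedures". It describes what follows once there is a SUSAR and is a cross-reference, so its silence on the SAEC sets no competing procedure.
- **A size taken from the serious-infection rate.** The 1.8% quoted under Drug related serious adverse reactions concerns a listed reaction. It says nothing about how often unexpected ones occur.

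**Conclusion.** The point holds as a conflict between stated rules. Three sections (Safety reporting, Reporting of serious adverse events/reactions, Reporting of SUSARs) make expedited reporting of an investigator's suspected reaction conditional on the SAEC. The SUSAR definition section makes all such suspected reactions subject to it. Following the first three, a suspected reaction can go without the 7-day or 15-day report.

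No count of affected events can be given, because the article states no rate of unexpected reactions and no rate of SAEC disagreement. The conclusion rests on two readings: that the investigator's mark expresses a suspicion, which the protocol's own description of the marked events supports, and that the conditional wording means what it says when the SAEC's answer is negative. That the SAEC can halt a report follows from that wording; no section says so outright. The article does not show that the SAEC is meant to have a veto or that any report would in fact be withheld. The change is worth making because the wording leaves the outcome undecided in the case where it matters.

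**What to change.** Reconcile Safety reporting, Reporting of serious adverse events/reactions and Reporting of SUSARs with the SUSAR definition section. State that:

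1. A serious event that is unexpected against the product information is expedited if either the reporting investigator or the SAEC suspects a causal relation to study drug.
2. An SAEC opinion that disagrees with the investigator is attached to the report and does not stop it.

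The SAEC keeps its review of all SAEs and can still identify SUSARs that a site did not mark.

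The cost is a wording change in the protocol and the SAEC's procedures, with possibly a few more expedited reports. Each of these would be unblinded by the CTEU before submission, as the protocol already requires for SUSAR reports.

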### Adverse reactions (AR)

An adverse reaction of an investigational medicinal product (AR) can be defined as all untoward and unintended responses to an investigational medicinal product related to any dose administered.

In the event an AR is reported during the trial, investigators will assess the severity of the adverse event using the following criteria, detailed on the adverse event report form in the case report form (CRF):

Mild: Awareness of signs or symptoms, but easily tolerated; are of minor irritant type; causing no loss of time from normal activities; symptoms would not require medication.

Moderate: Discomfort severe enough to cause interference with usual activities.

Severe: Inability to do work or usual activities; signs and symptoms may be of systemic nature or require medical evaluation and/or treatment.

#### Drug related adverse reactions

In all placebo-controlled trials conducted by Amgen, injection site reactions (ISRs) were frequently reported in the majority of patients (95% of which were reported to be mild to moderate in severity). ISRs included erythema, ecchymosis, inflammation and pain. On a dose of 100 mg/day, 71% of patients developed an ISR (n = 1565) compared to 28% of placebo treated patients (n = 733). The median duration of typical symptoms was 14 to 28 days. Other adverse events reported by patients administered with IL-1ra were, URI, headache, nausea, diarrhoea, sinusitis, arthralgia, flu like symptoms and abdominal pain. Allergic reactions reported in patients were rare.

Reported ISRs and other drug related adverse reactions will be reported on the adverse event report in the CRF. Patients reporting ISRs will be required to identify another injection site in which to administer the injection. Investigators will submit all adverse events reports for each patient to the CTEU at days 7, 14 and 30, three months and one year. The CTEU will maintain a log of all adverse reactions.

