#### Drug related serious adverse reactions

• Serious Infections – Previous trials conducted by Amgen demonstrated an incidence of serious infections in 1.8% of IL-1ra treated patients compared to 0.7% in placebo group. There were no on-study deaths due to serious infectious episodes.

• Neutropenia – Administration of IL-1ra was associated with neutropenia (ANC < 1.5 × 10^9^/I) in 2.4% of patients compared with 0.4% of placebo patients. None of these patients had serious infections associated with the neutropenia.

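### Non-serious clinical events are defined, graded, entered on the form and logged as drug-related reactions, while other sections speak of adverse events generally; the comparison by arm may be incomplete and is at risk of differential bias

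*Protocol article*

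**What the plan says.** Four statements in the protocol article tie non-serious events to drug relatedness:

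- **Definition** (Adverse reactions (AR)): the only non-serious category defined is the adverse reaction, "all untoward and unintended responses to an investigational medicinal product related to any dose administered".
- **Grading** (same section): "In the event an AR is reported during the trial, investigators will assess the severity of the adverse event". The trigger is a reaction, although the sentence then calls it an event.
- **Form content** (Drug related adverse reactions): "Reported ISRs and other drug related adverse reactions will be reported on the adverse event report in the CRF".
- **Central log** (same section): "The CTEU will maintain a log of all adverse reactions".

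Three statements carry no causality condition:

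- **Submission** (Drug related adverse reactions): "Investigators will submit all adverse events reports for each patient to the CTEU at days 7, 14 and 30, three months and one year".
- **Site co-ordinators' duties** (Study sites) include "recording adverse events, ensuring forms are sent to CTEU and that all edit queries are resolved".
- **Adjudication** (Clinical event review committee section): "The Clinical Event Review Committee will review adverse events during the study and adjudicate them to ensure the events meet the definitions given". This is done blind to arm.

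Serious events are handled differently. They are defined without reference to cause (Serious adverse events/reactions). A separate form takes any that are not on the listed outcomes, and the serious adverse events committee judges causality afterwards (Reporting of serious adverse events/reactions).

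**The concern.** If an event must be judged drug related before it is written down, the comparison of harms no longer rests on randomisation alone. It also depends on the site's opinion about each event. Here that opinion is formed by people who may have a clue to the arm: the research nurse gives the injections in hospital, investigators grade the reactions, and the protocol reports very different injection site reaction rates on active drug and placebo.

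Two things are at stake. Non-serious infections could be lost, in a trial of an IL-1 blocker in a new indication. The Background may encourage this, since it describes the drug as very safe and apparently free of infectious re-activation. In addition, sites that suspect active drug may attribute more readily, which would produce an excess that is not real. An event that was never recorded cannot be recovered at analysis.

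**Working it through.** The protocol gives no figure for event capture, so there is none to reproduce. The check has three parts.

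**1. Do the broader statements remove the causality condition?**

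- The submission sentence says when forms are sent. What goes on them is stated two sentences earlier in the same paragraph, as injection site and other drug related reactions.
- The site co-ordinators' duty is one item in a list and comes with no definition of an event.
- The review committee checks events against the definitions given. Those are the adverse reaction and the serious categories, and the committee can review only what has been recorded.

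These statements therefore do not clearly establish all-cause capture. If they are meant to, they conflict with the other four, and sites could apply different rules.

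**2. How informative is an injection site reaction about the arm?**

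Inputs: 71% on 100 mg/day and 28% on placebo (Drug related adverse reactions, from the manufacturer's other trials), and equal allocation (Study treatment). The rule is to guess active if a reaction is present and placebo if not.

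- Active given a reaction: 0.71 / (0.71 + 0.28) = 71.7%
- Placebo given no reaction: 0.72 / (0.72 + 0.29) = 71.3%
- Correct overall: 0.5 × 0.71 + 0.5 × 0.72 = 71.5%, against 50% by chance

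Carrying these rates over to 14 days in this population is an assumption. With placebo kept at 28%:

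- Active rate 50%: 0.5 × 0.50 + 0.5 × 0.72 = 61%
- Active rate 40%: 0.5 × 0.40 + 0.5 × 0.72 = 56%

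**3. What could attribution do to the recorded rates?**

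Assume the true non-serious event rate is the same in both arms. Let q1 and q0 be the probabilities that an event is called drug related in a patient with and without a reaction. The documents give neither, so both are assumed.

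Fraction of events recorded = P(reaction) × q1 + (1 − P(reaction)) × q0

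| q1 / q0 | Active | Placebo | Ratio |
|---|---|---|---|
| 50% / 50% | 0.500 | 0.500 | 1.00 |
| 50% / 40% | 0.71 × 0.5 + 0.29 × 0.4 = 0.471 | 0.28 × 0.5 + 0.72 × 0.4 = 0.428 | 1.10 |
| 60% / 30% | 0.71 × 0.6 + 0.29 × 0.3 = 0.513 | 0.28 × 0.6 + 0.72 × 0.3 = 0.384 | 1.34 |

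In the first row events are under-counted, but equally in both arms. If every event is recorded whatever its cause, the recorded rate equals the true rate in each arm and the ratio is 1.00.

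**Could serious events fill the gap?** The protocol cites an "incidence of serious infections in 1.8% of IL-1ra treated patients compared to 0.7% in placebo group". With 186 patients, 93 per arm, that is 93 × 0.018 = 1.7 against 93 × 0.007 = 0.7 expected cases, too few to inform a comparison.

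**The case against.** The strongest reply is that the text nowhere says only drug related events are recorded. A reader might infer a stated exclusion, but the article uses reaction and event interchangeably, and three of its statements speak of adverse events without qualification. This stands: the defect is a rule worded around reactions and not reconciled with broader wording elsewhere. It is not an express ban on recording other events.

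A reader might also infer that the whole safety comparison is compromised. The documents do not support that. Serious events are captured whatever the cause, MACE is followed up in all patients, and blood counts, creatinine and liver function are scheduled for everyone. A low neutrophil count would appear in the scheduled results even if no event were logged.

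The section also lists upper respiratory infection, sinusitis and flu-like symptoms among events seen with the drug. A site might treat those as reportable by name. That would narrow the gap, but the listing does not tell sites to record such events regardless of attribution.

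Finally, this is a condensed article, and the case report form and Manual of Operations are not shown. They may collect all events and hold relatedness as a separate field. That would be a full answer if the article were silent. It is not silent: it states what the form and the log contain, and any fuller document would have to depart from that statement.

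**Conclusion.** The point holds for non-serious clinical events. Read as written, the rules on definition, grading, form content and logging make recording depend on judged drug relatedness, so the comparison of these events by arm is incomplete on that reading and at risk of differential bias.

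It would go too far to call the comparison biased as a matter of fact. Differential bias requires attribution to vary with visible reactions, and the documents give no figure for that. The recorded ratio runs from 1.00 to 1.34 over the attribution rates assumed here; these values are illustrations, not bounds or estimates. The 71.5% chance of a correct guess rests on carrying over reaction rates from other trials, and falls to 56–61% at active rates of 40–50%.

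This is a cheap improvement. It does not affect the primary outcome, serious events, MACE or the scheduled laboratory tests.

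**What to change.** Reconcile the sections on adverse reactions, drug related adverse reactions, study sites and the clinical event review committee, so that:

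- every non-serious adverse event is recorded on the case report form whatever its judged cause, at the reporting times the protocol already sets (days 7, 14 and 30, three months and one year);
- relatedness is a separate field, completed after the event has been entered;
- the co-ordinating centre's log covers all adverse events;
- the between-arm table is based on all-cause events, with attributed events as a sub-row.

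The cost is a change of wording, a case report form field if it is not already there, and some extra data entry for about 186 patients at contacts already planned. The change has to be made before events occur.
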